### **Secondary Outcome:**

#### **1. Cognitive, Affective and Psychomotor perceived learning Improvement:**

Improvement in the cognitive, affective and psychomotor domain of CAP perceived learning competency scale on postintervention score of experimental group will signify positive impact of intervention.

---

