#### OBJECTIVES

1. To assess the effect of game-based learning as an innovative self-directed learning strategy on knowledge acquisition among nursing undergraduates.
2. To assess the effect of conventional learning method on knowledge acquisition among nursing undergraduates.
3. To evaluate the effect of game-based learning as an innovative self-directed learning strategy on self-directed learning abilities among nursing undergraduates.

4. To evaluate the effect of conventional learning method on self-directed learning abilities among nursing undergraduates.
5. To compare the impact of game-based learning and conventional learning method on knowledge acquisition among nursing undergraduates after 12 weeks of intervention.
6. To determine whether game-based learning is superior to conventional learning in improving self-directed learning abilities in nursing undergraduates after 12 weeks of intervention.

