##### INTERVENTIONS

Researcher will provide detailed information about purpose and procedures of the study to the participants. They will be ensured for the anonymity of participants' personal information and collected data. Participants will be made aware of approximate time needed to complete the questionnaire (around 15-25mins). They will be informed that there will be no penalty for not participating and they can withdraw at any time during the study. They will be assured that their responses would not have any effect on their academic ground and it will be kept confidential with researcher. A written informed consent will be taken from the subjects willing to participate in the study.

After signing an informed consent form, participants will undertake a pretest covering knowledge, self-directed learning abilities, and perceived learning competency. Following that, two batches of students on the basis of their academic semester will participate in a 90-minute structured teaching session on self-directed learning, where the students will be

engaged in group activity and the concept of self-directed learning, its importance and process will be discussed with them.

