## STATISTICAL METHODS

The study will use SPSS version 21, with tests like Shapiro-wilk, skewness, and kurtosis to evaluate the normal distribution of variables. Pre-test homogeneity will be assessed using descriptive statistics, independent t-tests, chi-square tests, and Fisher's exact test. ANOVA will compare differences in SDL ability, PL competency, and knowledge between groups. Regression analysis will explore the relationship between independent variables and dependent outcomes. Differences between pre-test and post-test will be analyzed using paired t-test. All statistical analysis will be two-sided, with a p-value less than 0.05 considered statistically significant.

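### The secondary-outcome criterion counts improvement in the game arm alone as a positive impact, without reference to the control arm

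*Protocol*

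**What the plan says.** In the Protocol, Outcomes, Secondary Outcome, improvement on the CAP "scale on postintervention score of experimental group will signify positive impact of intervention". The sentence mentions neither the control arm nor a test, threshold or time point.

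The neighbouring text differs. The two primary outcomes, SDL abilities and knowledge, are both defined by a difference between the experimental and control groups. Objectives 5 and 6 are also comparative; Objective 5 reads "To compare the impact of game-based learning and conventional learning method on knowledge acquisition among nursing undergraduates after 12 weeks of intervention". They cover knowledge and SDL abilities, and no objective mentions CAP.

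Objectives 1 to 4 each take one arm on its own. Objective 1 is "To assess the effect of game-based learning as an innovative self-directed learning strategy on knowledge acquisition among nursing undergraduates" and Objective 3 is "To evaluate the effect of game-based learning as an innovative self-directed learning strategy on self-directed learning abilities among nursing undergraduates". Objectives 2 and 4 put the same questions for the conventional arm.

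Statistical Methods lists two relevant analyses: an ANOVA between groups covering SDL ability, perceived learning (PL) competency and knowledge, and, separately, "Differences between pre-test and post-test will be analyzed using paired t-test". All tests are two-sided at 0.05.

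**The concern.** A change within one arm of a randomised trial mixes the effect of that arm's intervention with everything else that happens between the two measurements. This protocol builds in several shared sources of change:

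- After the pretest and before allocation, "two batches of students on the basis of their academic semester will participate in a 90-minute structured teaching session on self-directed learning" (Interventions). Everyone attends.
- The control is active: material on the same topic, an hour of self-study with an immediate post-test, then four weeks of encouraged self-learning.
- All participants are offered weekly Zoom guidance on self-directed learning for a month (Strategies to Improve Adherence).
- The same inventory is given four times (Data Collection Methods).

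Perceived learning can therefore rise in the game arm for reasons that apply equally to the control arm. Followed as written, the criterion would credit the game with a benefit in a trial where it adds nothing over self-study. It also leaves two routes to a CAP conclusion that can disagree: the single-arm criterion in Outcomes and the between-group ANOVA in Statistical Methods.

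**Working it through.** **1. The plan's own figure.** Sample Size assumes an effect size of 0.5, significance level 0.05 and 80% power, and states 64 per arm. The two-sided two-sample t-test (noncentral t) gives n = 63.77, rounded up to 64, with power 80.1%. The figure reproduces, and it is a between-group calculation. The planned 70 per arm less 10% dropout leaves 70 × 0.9 = 63 completers.

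**2. Inputs for the check.**
- From the protocol: 63 to 64 completers per arm; two-sided 0.05; paired t-test for pre/post differences.
- Assumed, because the protocol gives no value: the same true gain g (in SD units) in both arms, so the true game effect is zero; pre/post correlation r between 0.3 and 0.7; equal SD before and after.
- Inferred: that improvement in the Secondary Outcome sentence would be judged by the paired t-test.

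**3. Formula.** The SD of the change is √(2(1 − r)) in units of the score SD, so the standardised change is dz = g / √(2(1 − r)). The chance of a significant paired test is its power at dz with n pairs.

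Example: g = 0.3 and r = 0.5 give dz = 0.3 / √1 = 0.30; with n = 64 the power is 66%.

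**4. Chance that the game arm shows a significant gain when the game adds nothing.**

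| Shared gain g | r = 0.3 (n = 63 / 64) | r = 0.5 (n = 63 / 64) | r = 0.7 (n = 63 / 64) |
|---|---|---|---|
| 0.2 SD | 26% / 27% | 35% / 35% | 52% / 53% |
| 0.3 SD | 51% / 52% | 65% / 66% | 86% / 86% |
| 0.5 SD | 91% / 91% | 97% / 98% | 99.9% / 99.9% |

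**5. The between-arm test under the same conditions.** In a simulation of 20,000 trials (64 per arm, r = 0.5, equal gains in both arms), comparing the change between arms rejected in 5.0%, 4.9% and 4.9% of trials at gains of 0.2, 0.3 and 0.5 SD. It rejected in favour of the game in 2.5%, 2.4% and 2.2%. The shared gain cancels in the contrast, so the rate does not depend on g.

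**6. Sensitivity to the larger enrolment.** Sample Size also mentions one hundred per group. With n = 100 and r = 0.5 the within-arm figures rise to 51%, 84% and 99.9%. More participants make the single-arm criterion easier to meet, not safer.

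**The case against.** The strongest reply is that the trial's main claims are already comparative. The hypotheses, the aim, Objectives 5–6, the superiority design, the sample size and both primary outcomes all set one arm against the other, and Statistical Methods includes PL competency in a between-group ANOVA. All of this stands. A reader might infer that the plan discards its randomised control; the documents do not support that.

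The sentence also names no test or significance criterion, so the rule simulated above is partly an inference. That stands too, and the percentages are conditional on it. The defect in the wording does not depend on it: under any test, a single-arm improvement cannot separate the game from the shared exposures.

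A reader might also take Objectives 1–4 as four claims of efficacy. They do not mention pre/post change and carry no test or decision rule, and the comparisons for knowledge and SDL abilities are stated separately. Objectives 2 ("To assess the effect of conventional learning method on knowledge acquisition among nursing undergraduates") and 4 ("To evaluate the effect of conventional learning method on self-directed learning abilities among nursing undergraduates") concern the conventional arm and could not show an effect of the game. Their wording is loose, but they are not the core of the problem. Nor does the protocol propose to read significance in one arm and not in the other as a difference, so that error cannot be charged to it.

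Finally, the paired t-test keeps its 5% error for its own null hypothesis of no change. The inflation arises only when its result is read as an impact of the game, which is how the Secondary Outcome sentence invites a reader to take it.

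**Conclusion.** The point holds for the secondary-outcome criterion. It is wrong as written and out of line with both the primary outcome definitions and the between-group ANOVA in the same protocol. The false-positive figures in the working rest on the paired t-test reading and on assumed gains and correlations. It would be too strong to say that the criterion is bound to show an effect: that is nearly true for shared gains of about 0.5 SD or more, while at 0.2 SD it is a rate of roughly a quarter to a half. Even so, every case examined is far above the 2.5% in favour of the game that a two-sided between-arm test allows.

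The primary outcomes and Objectives 5–6 are untouched. Because the defect lies in one secondary criterion, with loose wording in Objectives 1–4, and a suitable comparison is already listed, the severity is moderate.

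**What to change.** - **Secondary Outcome:** define impact on CAP as the between-arm difference in post-intervention score, adjusted for baseline, with a 95% CI and at a time point that the sponsor names. This brings it into line with the between-group comparison in Statistical Methods.
- **Objectives 1–4:** reword them as describing the change within each arm.
- **Statistical Methods:** state that the paired t-tests are descriptive and that claims about the game rest on between-arm contrasts.

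The cost is protocol wording and the ethics committee approval that the protocol requires for amendments. CAP is part of the inventory already given to both arms, so no new data, visits or participants are needed.

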## PARTICIPANT TIMELINE

A schematic diagram presenting enrolment, random allocation, intervention, follow-up and data analysis of the study is shown below;

[figure not shown]

Figure 2. Schematic diagram for study

## DATA COLLECTION METHODS

The researcher will use a structured and pre-tested data collection inventory to gather study data. The data will be entered into the study database promptly. After obtaining written consent, a self-administered inventory will be distributed and collected from students. Data collection will occur at four time points: preintervention, immediately postintervention, 4 weeks postintervention, and 12 weeks postintervention using the same inventory.

Data collection inventory comprises of four sections;

A. **Socio-demographic information:** age, gender, semester, place of residence and previous exposure to game-based learning.

B. **Knowledge questionnaire:** A 15-item multiple-choice questionnaire on antimicrobial resistance, antimicrobial stewardship, and infection control will be used to assess knowledge. The score ranges from 0-15, with scores categorized as adequate knowledge (above 75%), moderately adequate knowledge (between 51-75%), and inadequate knowledge (less than 50%). Each item will be tested for validity and reliability before the study.

Expert evaluation will confirm content validity, with a panel of subject matter experts assessing relevance, clarity, and alignment with study objectives. Cronbach's alpha will be used to determine internal consistency, with a Cronbach's alpha value of 0.70 or higher indicating acceptable reliability. Test-retest reliability will be assessed by administering the questionnaire to a sample of participants at two different time points (with an interval of two weeks). Intraclass correlation coefficients (ICC) will be used to assess results' consistency over time, with an ICC value greater than 0.75 indicating strong reliability.

C. **Self-Directed Learning Instrument (SDLI):** The Self-Directed Learning Instrument (SDLI) is a reliable tool developed by Cheng et al. (2010) with good internal consistency (Cronbach's total scale was  $\alpha = 0.916$ ). Cadorin L et al. (2017) recommend SDLI for assessing SDL abilities among nursing students and nurses due to its excellent methodology quality, Cronbach  $\alpha$  ranging from 0.73 to 0.91, and structural validities. Content validity was supported by two rounds of Delphi study. It is comprised of 20 items categorized into four domains:

- a. Learning motivation: six items ( $\alpha = 0.80$ ),
- b. Planning and implementing: six items ( $\alpha = 0.86$ ),
- c. Self-monitoring: four items ( $\alpha = 0.78$ ), and
- d. Interpersonal communication: four items ( $\alpha = 0.76$ ).

The Self-directed learning instrument (SDLI) metric uses a five-point Likert scale to measure self-assessment of self-directed learning (SDL) abilities. Scores range from 1 to

5, with "strongly disagree" indicating very low level of (self-assessed) abilities, and "strongly agree" indicating high level of (self-assessed) SDL abilities. All the statements are stated positively and the total possible score ranges from 20 to 100, with higher scores indicating higher SDL abilities.

- D. **Cognitive, Affective & Psychomotor (CAP) perceived learning scale:** The study will utilize the CAP Perceived Learning Scale, a nine-item, 6-point Likert scale, developed by Rovai et al. (2009), to measure perceived cognitive, affective, and psychomotor learning in game-based and conventional learning environments. The scale is a reliable and valid tool with internal consistency of 0.79 and supported concurrent validity. It generates an overall score representing perceived learning across three domains: cognitive learning, affective learning, and psychomotor learning.

Subscale cognitive learning describes a students' ability to recall or recognition of knowledge, affective learning is the positive attitude towards the subject matter, and psychomotor learning is the capacity to perform tasks (Rovai et al., 2009). In CAP Perceived Learning Scale, statements 1,2 and 5 measures perceived cognitive learning; statement 4,6, and 9 measures perceived affective learning and statement 3, 7, and 8 measures perceived psychomotor learning. Statement two and seven are inversely scored while the other statements are scored in a standard pattern. Total scores can range from a maximum of 54 to a minimum of 0 and CAP subscale scores can range from maximum of 18 to minimum of 0. A high CAP Perceived Learning Scale score is an indicator of a keen perception of learning by students participating in the study (Rovai et al., 2009).

Self-directed learning instrument (SDLI) and CAP Perceived learning Scale will be used for the study in its original form without any modification. Participant information with personal identifiers will be stored in paper-based form in a locked filing cabinet in a secure and locked private space. To ensure accuracy and completeness, study data will be reviewed by the researcher.

---

#### DATA MANAGEMENT & MONITORING

The study will use SPSS software for data management, including entry, validation, coding, cleaning, and preparing the final database. The researcher will maintain and store study records, including informed consent. The Data Monitoring Committee (DMC) is not essential due to nature, scale, and resources availability. Alternative monitoring measures will be implemented to ensure scientific and ethical integrity. Data management will comply with institutional ethics committee for participant protection and confidentiality. Regular review of trial progress will ensure data quality and accuracy.

## STATISTICAL METHODS

The study will use SPSS version 21, with tests like Shapiro-wilk, skewness, and kurtosis to evaluate the normal distribution of variables. Pre-test homogeneity will be assessed using descriptive statistics, independent t-tests, chi-square tests, and Fisher's exact test. ANOVA will compare differences in SDL ability, PL competency, and knowledge between groups. Regression analysis will explore the relationship between independent variables and dependent outcomes. Differences between pre-test and post-test will be analyzed using paired t-test. All statistical analysis will be two-sided, with a p-value less than 0.05 considered statistically significant.

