## METHODS

### STUDY DESIGN

It is a prospective, randomized, controlled, data analyst-blinded, single centric superiority study with two parallel groups allocated at a 1:1 ratio and follow-up period of 12 weeks to identify the impact of self-directed learning strategy using educational games as an innovative learning method for nursing students in the experimental group compared with the conventional learning group as control.

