#### **SAMPLE SIZE**

The study hypothesize that the self-directed learning abilities and knowledge acquisition among participants attending the game based learning would be superior to those attending the conventional learning. The sample size is determined using G\*Power (Version 3.1.9.7). Assuming a significance level of 0.05 and effect size of 0.5 (based on meta-analysis study\* which estimated a medium effect size in favor of game-based learning over learning without gamification), 64 participants per arm will be required to achieve a statistical power of 80%. Considering a dropout rate of 10%, 70 participants per arm, 140 participants in total, is required.

- Census sampling will be done to eliminate the selection bias. All the basic Bsc.Nursing students from two semester will be enrolled in study with hundred in each experimental and control group. Total 200 students is planned to be enrolled.

---

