#### ASSIGNMENT OF INTERVENTIONS (FOR CONTROLLED TRIALS)

##### ALLOCATION

##### SEQUENCE GENERATION

Researcher will use computer-generated random numbers to allocate participants to one of the two groups. The randomization method employs block randomization with block size of 4 and 8. Stratification is based on the semester of their study, as this factor may influence the study outcome. Independent personnel not involved in the study will utilize random sequence generator software to generate a random sequence, randomly allocating subjects in a 1:1 ratio and dividing them into two groups.

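### The between-group ANOVA adjusts for neither the pre-test score nor the semester stratum, which gives away precision that the collected data could supply at no cost

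*Protocol*

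**What the plan says.** The between-group analysis is one sentence in Statistical Methods: "ANOVA will compare differences in SDL ability, PL competency, and knowledge between groups". No covariate or stratification term is attached to it. In that section the pre-test is otherwise used in two ways. One is a comparability check: "Pre-test homogeneity will be assessed using descriptive statistics, independent t-tests, chi-square tests, and Fisher's exact test". The other is paired t-tests of pre-test against post-test. Regression is listed for exploring relationships, with no variables named.

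Under Interventions, students complete a pre-test on knowledge, self-directed learning ability and perceived learning after consent and before allocation. Under Sequence Generation, randomisation uses blocks of 4 and 8, and "Stratification is based on the semester of their study, as this factor may influence the study outcome". The text after the self-directed learning module table describes the same allocation as simple random sampling from a randomisation list.

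The Outcomes section describes the two primary outcomes differently. For the self-directed learning score (SDLI), it refers to pre/post differences compared between groups. For knowledge, it refers to a difference in scores between groups and does not mention the pre-test.

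**The concern.** The protocol collects one variable that is likely to predict the outcome (the pre-test) and itself identifies another that may do so (semester). It enters neither in the comparison that decides the trial.

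- If post-scores are compared, a chance pre-test difference between arms stays in the estimate.
- If change scores are compared, baseline is subtracted with a fixed coefficient of 1 rather than the coefficient the data support. This adds noise when the pre/post correlation is low.
- Testing for homogeneity at baseline alters neither estimate.
- When randomisation is balanced within strata and the stratum predicts the outcome, an analysis without the stratum reports a larger standard error than the design delivers.

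At stake are the width of the confidence intervals, the power for both primary outcomes, and the freedom to choose between post-score and change-score analysis after the data are seen.

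**Working it through.** **Inputs from the protocol.** "Assuming a significance level of 0.05 and effect size of 0.5" (Sample Size); "All statistical analysis will be two-sided, with a p-value less than 0.05 considered statistically significant" (Statistical Methods); "two parallel groups allocated at a 1:1 ratio" (Study Design); "64 participants per arm will be required to achieve a statistical power of 80" per cent, and "Considering a dropout rate of 10%, 70 participants per arm, 140 participants in total, is required" (Sample Size).

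**Assumed, because the documents do not give them.** The pre/post correlation r (0.3 to 0.7), equal variances at the two time points, and the size of any semester difference. The effect of 0.5 is taken in post-score SD units.

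**The plan's own figure.** A two-sample t-test with two-sided alpha 0.05, d = 0.5 and 80% power (noncentral t) needs 63.77, so 64 per arm, with power 0.801. The stated figure reproduces as an unadjusted comparison. For dropout, 64 × 1.1 = 70.4, close to the stated 70. Losing 10% of 70 leaves 63 completers per arm.

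**Baseline.** Variance relative to a post-score ANOVA:
- change score: 2(1 − r)
- baseline-adjusted (ANCOVA): 1 − r²
- ratio of change score to ANCOVA: 2/(1 + r), which exceeds 1 for every r below 1

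Power at 63 per arm is the t-test power with d = 0.5 divided by the square root of the factor. At r = 0.5, for example, ANCOVA uses 0.5/√0.75 = 0.577.

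| r | Change-score factor | ANCOVA factor | Power, post-score | Power, change score | Power, ANCOVA |
|---|---|---|---|---|---|
| 0.3 | 1.40 | 0.91 | 79.5% | 65.3% | 83.1% |
| 0.5 | 1.00 | 0.75 | 79.5% | 79.5% | 89.5% |
| 0.6 | 0.80 | 0.64 | 79.5% | 87.6% | 93.6% |
| 0.7 | 0.60 | 0.51 | 79.5% | 94.9% | 97.4% |

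The effect detectable with 80% power is 0.50 SD unadjusted. With adjustment it is 0.44, 0.40 and 0.36 SD at r = 0.5, 0.6 and 0.7. In simulation with 64 per arm and no semester effect, ANCOVA power was 0.825, 0.901 and 0.974 at r = 0.3, 0.5 and 0.7, in line with the formula (0.837, 0.900 and 0.976).

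**Semester.** With two equal strata that differ by δ within-stratum SDs, the share of post-score variance due to semester is R² = (δ²/4)/(1 + δ²/4). At δ = 0.5 this is 0.0625/1.0625 = 5.9%. The reported standard error divided by the true one is 1/√(1 − R²) = 1/√0.941 = 1.031, so it is about 3% too large, and the true type I error is about 0.043. For R² of 0.05, 0.10 and 0.20, the excess is 2.6%, 5.4% and 11.8%, and the type I error is 0.044, 0.039 and 0.028. In simulation, a change-score ANOVA without semester kept its level (0.046 to 0.055) when semester shifted both time points equally.

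**Overlap of the two adjustments.** Suppose a 0.5 SD semester gap shifts pre- and post-scores alike. Residual variance after baseline alone is 1.0625 − (r + 0.0625)²/1.0625. Adding semester takes it to 1 − r². At r = 0.5 that is 0.765 to 0.750, and at r = 0.7 it is 0.515 to 0.510: a fall of 1.9% and 1.0%. Most of the 5.9% is then already captured by baseline.

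**The case against.** The case for leaving the sentence alone has several parts.

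- **The pre-test is not plainly unused.** The SDLI outcome is worded as a pre/post difference between groups, and the ANOVA sentence can be read the same way. This stands. A reader might infer that the pre-test is ignored altogether, but the text does not support that for SDLI. What it supports is that the pre-test is not a covariate, and that the choice between post-score and change score is left open, most clearly for knowledge.
- **The standard error is not dangerously wrong.** A reader might infer a false-positive risk from the missing stratum term. The direction is the opposite. The test is conservative, only if semester predicts the analysed outcome, and only slightly so at modest gaps. This assumes independent students. The experimental arm plays in small teams, and correlation within teams would act in the other direction; that is a separate matter.
- **The planned power is met without adjustment.** This is true for a post-score ANOVA, which is what the sample size assumes. It is not true for a change-score ANOVA if r is below 0.5. The Sample Size section also mentions enrolling 100 per arm. With 90 completers per arm, unadjusted power is already about 92%, so the power gain would be smaller, although intervals would still narrow.
- **Students with a missed visit would be dropped.** A reader might infer a clash with the intention-to-treat statement through listwise deletion in a repeated-measures ANOVA. The protocol names no repeated-measures ANOVA, so no such clash is shown.
- **Covariates can be left to an SAP.** This is often so. Here, however, the protocol itself names the method, and the method as named carries no adjustment.

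**Conclusion.** The point holds as a matter of efficiency and clarity. It is not a flaw that invalidates the trial. As written, the ANOVA uses neither the pre-test as a covariate nor the semester stratum, and it does not settle whether post-scores or change scores are compared. Baseline adjustment has lower variance than both for any correlation strictly between 0 and 1.

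At 63 per arm and d = 0.5, adjustment raises power from 79.5% to between 83% and 97% for assumed correlations of 0.3 to 0.7. A change-score ANOVA ranges from 65% to 95% over the same values and misses the 80% target if the correlation is low. The semester term matters less: about 3% in the standard error at an assumed 0.5 SD gap, in the conservative direction, and partly duplicated by baseline. All these sizes depend on the assumed correlations and semester gap. The ordering of the three methods does not.

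**What to change.** Replace the ANOVA sentence with a model for each outcome that includes arm, the pre-test score of that outcome and semester. Report the adjusted arm difference with its 95% CI. Either of two forms will do:

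- an ANCOVA of the 12-week score, the time point named in objectives 5 and 6; or
- a linear mixed model over the post-baseline visits with arm-by-visit terms and the 12-week contrast as primary, which also keeps students with partial follow-up.

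Reconcile Sequence Generation (blocks stratified by semester) with the text after the module table (simple random sampling), so that the stratum term matches the randomisation actually used. Adjustment for the pre-test is worthwhile under either description.

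The cost is a few lines of wording and the ethics committee approval that the protocol requires for any amendment. No new data or software are needed. Whether to keep the baseline significance tests is a reporting preference and not part of this point.
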